#### Individual lifestyle counseling

The individual lifestyle counseling consists of six to eight sessions in the 1st 6 months, followed by 3 to 4 booster sessions in the next 1.5 years, and it aims at both diet and PA. We use motivational interviewing (MI) as a counseling strategy, taking into account dietary habits and cultural norms regarding diet and PA. Motivational interviewing can be defined as “a client-centered, directive method for enhancing intrinsic motivation to change by exploring and resolving ambivalence” 
[40]. Motivational interviewing is an upcoming intervention methodology, and the evidence for MI for lifestyle advice seems to be promising 
[41,42].

The six dieticians who will conduct the lifestyle counseling are familiar with the Hindustani Surinamese culture and dietary habits. The medical psychologist who trained the dieticians in MI is an expert in MI 
[43]. Special attention will be paid to possible barriers and stimulating factors that are specific to the Hindustani Surinamese population. As recommended, we will provide continued support for MI to achieve optimal results in appliance and effects 
[44].

#### Family session and cooking classes

Besides the individual sessions, participants will also be offered a family session with the dietician. The purpose of this session is to decrease the social pressure to eat unhealthily and to increase the social support for a healthful lifestyle for the family. This entails providing product information and discussing the importance of a healthful lifestyle and how to increase support.

The participants will be offered two cooking classes to increase their self-efficacy in skills that they can learn for adjusting traditional dishes in a more healthful way. They will be encouraged to bring spouses or close relatives with them to increase their knowledge and attitude towards healthful diet.

#### Exercise on prescription

The intervention group will be offered “exercise on prescription” (EoP), a 20-week supervised PA program, which has previously been described 
[45-47]. The participants can choose between aquarobics and fitness, offered in men-only or women-only groups 
[45,46]. Trained PA coaches will monitor and supervise the participation. At the end of the 20 weeks, a final evaluation will take place, at which time the lifestyle advisor will provide information about low-budget sport locations.

### Control group

The participants in the control group will be invited to join two group sessions led by student dieticians (after baseline measurements and after 6 months). The student dieticians will provide generic information about diabetes, discuss the current guidelines for diet and PA, list methods for achieving the recommended PA, and present some cases. In the second session, one respondent will be given the opportunity to become a case study. In addition, the control group will receive two flyers (at 3 months and 9 months) with simple, generic lifestyle advice. Both flyers offer participants a chance to phone in during preset hours to obtain personal advice from a dietician.

### Data collection

For both the intervention group and the control group, the baseline (T_0_) and subsequent measurements after 1 (T_1_) and 2 years (T_2_) of the trial include blood sampling [fasting and 2-hour OGTT (glucose load 75 g)], a structured face-to-face interview, and a physical examination. These actions all took place, and will take place again, in one central health care center in The Hague. The participants will receive a questionnaire after 6 months as part of the process evaluation. Participants who do not fill in the questionnaire at 6 months will be asked to complete it at T_1_ in the health care center. Table 
1 shows the measures recorded at baseline and to be recorded again after 6 months, 1 year, and 2 years. Participants who were not reached and any participants who indicate that they intend to quit the trial at T_1_ or T_2_ will be offered a brief home visit instead of the more extensive screening at the health care center (Table 
1).

#### Laboratory assessments

Plasma glucose, insulin, and Hb_A1c_ levels and other biomarkers will be assessed (Table 1). All laboratory assessments will be carried out according a standardized protocol at the General Practice Laboratory Foundation, Etten-Leur, The Netherlands. At different time points, material is stored at −80°C for future analyses (Table 
1).

#### Physical examination

Trained research staff carries out the physical examinations in a standardized protocol. A Seca mechanical scale (Seca 761, Seca, Hamburg, Germany) is used to weigh the participants (wearing light clothing) to the nearest 500 g. Height is recorded to the nearest 0.01 m on a Seca portable stadiometer (Seca 214, Seca, Hamburg, Germany), and waist and hip circumferences are determined to the nearest 0.01 m with a tape measure. A bioelectrical impedance analysis (OMRON BF500, Omron Healthcare, Hoofddorp, The Netherlands) is used to determine body fat to the nearest 0.1%. All anthropometric measurements are obtained twice – we allowed differences between two measurements of 2 cm, 2 kg, or 2% – and the means will be used for analysis.

The participant is in the seated position when the blood pressure (Omron M5-1, Omron Healthcare, Hoofddorp, The Netherlands) is measured on the nondominant arm supported at heart level. At most, five measurements are taken. We calculate the mean from the first two measurements with less than 5 mm Hg difference in both systolic and diastolic blood pressure 
[49]. We assess cardiorespiratory fitness with the Chester STEP test 
[28,29].

#### Structured face-to-face interview

##### Behavioral outcomes

We will assess PA with the Short Questionnaire to Assess Health-enhancing Physical Activity (SQUASH), supplemented with ethnicity-specific activities [22,23]. Dietary intake will be determined with questions based on the national guideline for a healthful diet, supplemented with questions about specific dietary habits of the Hindustani Surinamese population 
[34,38]. We will assess fruit, vegetables, rice, and bread consumption with multi-item measurements to determine the quantity and frequency (*n* = 3, *n* = 2, *n* = 2, and *n* = 11, respectively), and two single-item questions will address the use of breakfast and the regularity of the meals. We will also measure the current smoking and alcohol consumption (Table 
1) 
[24,25].

##### Intermediate outcome measures

Health-related quality of life will be measured with short form (SF)-12 and three extra emotional status questions from SF-36 
[30,31]. We will measure distress with the 16 distress questions of the Four-Dimensional Symptom Questionnaire (distress, depression, anxiety, and somatization) 
[32].

We will measure personal vulnerability with a three-item personal vulnerability score 
[33] and risk perception with 12 statements about the participant’s perceived risk of diabetes in connection with overweight, current smoking, and/or unhealthy eating. The statements are based on general risk factors and information from focus group discussions 
[37,50].

We will determine attitudes towards PA and diet directly with questions about importance and joy regarding several aspects of PA and diet (e.g., PA in leisure time; breakfast; fruit, vegetable and whole grain intake). We will assess attitude towards PA indirectly with seven items about the possible consequences of increasing PA (e.g., “If I increase my PA, I will look better”).

We will ask whether the spouse, other family members, or close relatives encourage the respondent to be physically active (*n* = 3). Moreover, we will measure overall support towards the targeted aspects of diet (*n* = 7).

We will measure self-efficacy expectations towards diet change and dealing with specific PA barriers with five items about PA and seven items about aspects of diet [focus group discussions; unpublished data].

The stage of change towards PA and diet will be measured with the algorithm described in the Transtheoretical Model 
[51]. This includes three scales regarding motivation to change, described as: unmotivated to change diet and PA within 6 months, motivated to change at least parts of the diet and PA within 6 months, and prepared to change within 1 month 
[52].

##### Background characteristics

We will assess physical health, religion, and socioeconomic status (as indicated by educational level, source of income, and net family income) using questions similar to those of the SUNSET study 
[26,27].

### Activities to encourage participation in the data collection

We will send all participants the DH!AAN study newsletter twice a year in order to inform them of the progress of the study and to encourage continued participation. The participants were rewarded with a gift coupon of €5 to €10 for their participation in the baseline measurements; this reward will be repeated for subsequent measurements. Moreover, a prize in the form of a trip to Suriname will be raffled to one of the participants of the T_1_ and T_2_ measurements.

### Statistical analysis

#### Size of the study population and the power calculation

The Online supplement (Additional file 
1) describes the original power calculation. Here we calculate the power of the study to demonstrate differences in the main outcomes using the numbers of participants in the intervention and control groups.

A total of 536 participants were included in the RCT with a minimum of 253 participants per group. Previous studies found a difference in weight reduction of 1.5–3 kg (SD of 4) [10,53], and a difference in FPG of 0.2–0.35 mmol/l (SD of 0.7) [10,53]. Assuming a an alpha of 5%, and a dropout rate of 30%, we have a power of 86% or more to demonstrate a minimum difference in weight reduction of 1.25 kg and a change in glucose level of 0.2 mmol/l with our data.

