##### Participation in the randomized controlled trial

In total, 536 people (283 intervention group; 253 control group) were included in the RCT (Figure 
2). Of all the people considered at high risk of DM (*n* = 1045), 158 (15.1%) actively declined to participate. Moreover, 89 people (8.5%) were found not eligible; 67 prior to the randomization and 22 during the baseline measurement because of suspected DM. The net participation rate in the trial was 56.1% (536 of those eligible (n = 956)).

The characteristics of the participants, as measured in the initial screening, were comparable with the characteristics of the nonparticipants, with the exception of family history of DM and education (Table 
2). Participants more often reported having a family member with DM than nonparticipants (chi-squared test, *p* = 0.043). Moreover, the participants had a somewhat higher level of education than the nonparticipants (Mann–Whitney *U* test, *p* = 0.023). Nonparticipants seemed to have a higher blood pressure and were more likely to be classed as having elevated fasting glucose, but this was not significant.

**Table 2 T2:** Determinants of participation for those eligible for the trial

	**All eligible people**	**Participants**	**Nonparticipants**	**Significance***
	***n*** **= 956**^**^**^	***n*** **= 536**	***n*** **= 420**	
Median age in years	44 (36–51)	45 (37–52)	44 (35–51)	0.13
Men (%)	468 (49.0)	265 (49.4)	203 (48.3)	0.73
18–34 years (%)	212 (22.2)	109 (20.3)	103 (24.5)	
35–44 years (%)	280 (29.3)	159 (29.7)	121 (28.8)	
45–60 years (%)	464 (48.5)	268 (50.0)	196 (46.7)	
Education (%)				0.02**
Elementary^a^	126 (13.6)	61 (11.7)	65 (16.1)	
Intermediate^b^	645 (69.8)	364 (70.0)	281 (69.6)	
University or equivalent^c^	153 (16.6)	95 (18.3)	58 (14.4)	
Relatives with DM (%)^d^	685 (73.7)	398 (76.2)	287 (70.3)	0.04**
Median weight in kg	73.5 (64.8–82.0)	73.3 (65.0–82.1)	73.8 (64.0–82.1)	0.90
Median BMI in kg/m^2^	26.8 (24.4–29.9)	26.8 (24.5–29.7)	26.7 (24.1–30.3)	0.98
Overweight: ≥ 23 kg/m^2^ (%)^e^	419 (44.9)	246 (46.9)	173 (42.3)	0.17
Obesity: ≥ 27.5 kg/m^2^ (%)^e^	412 (44.1)	227 (43.2)	185 (45.2)	0.54
Median SBP in mm Hg	128.0 (119.0–38.0)	127.0 (118.0–137.0)	129.0 (120.0–0.0)	0.07
Median DBP in mm Hg	83.0 (76.0–90.0)	82.0 (76.0–90.0)	84.0 (76.0–92.0)	0.06
Hypertension (%)^f|^	62 (38.4)	196 (37.1)	166 (40.1)	0.34
Median FPG (mmol/l)	5.3 (4.9–5.7)	5.3 (4.9–5.7)	5.4 (5.0–5.7)	0.61
Elevated FPG^†^(%)	332 (34.8)	174 (32.5)	158 (37.9)	0.08

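### One power figure of at least 86% covers both weight and glucose with sidedness unstated; under a two-sided 5% test it fits weight only, and glucose has about 79%

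*Protocol article*

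**What the plan says.** The section on study population size and power recalculates power for the sample already recruited, "using the numbers of participants in the intervention and control groups". It notes that "A total of 536 participants were included in the RCT with a minimum of 253 participants per group"; the section on participation in the trial gives the split: "536 people (283 intervention group; 253 control group) were included in the RCT".

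The effect sizes and SDs come from previous studies. For weight, the cited range is 1.5–3 kg with an SD of 4. For glucose it is "a difference in FPG of 0.2–0.35 mmol/l (SD of 0.7" mmol/l). The remaining assumptions are given as "Assuming a an alpha of 5%, and a dropout rate of 30" percent. The result is a single statement for both outcomes: "we have a power of 86% or more to demonstrate a minimum difference in weight reduction of 1.25 kg and a change in glucose"; the glucose target is 0.2 mmol/l.

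The study design section lists weight change and mean blood glucose concentration among the primary outcomes. The article nowhere says whether the 5% is one-sided or two-sided.

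**The concern.** The two targets are not equally hard to detect. In SD units, weight is 1.25/4 = 0.313 and glucose is 0.2/0.7 = 0.286. With the same numbers analysed and the same alpha, glucose must have the lower power. One lower bound can cover both only if it is true for glucose.

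Under the usual two-sided reading of a 5% alpha, the stated figure matches weight and clearly misses glucose. A reader who assumes that convention would take a null glucose result to come from a test with at most a 14% chance of missing a 0.2 mmol/l difference. On the stated inputs that chance would be 21–24%. The limitations section says the focus moved from diabetes incidence to other outcome measures, so the glucose result carries more of the trial's message than it otherwise would.

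**Working it through.** **Inputs** (all from the power section, except the arm sizes, which come from the section on participation in the trial)

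- Arms 283 and 253. After 30% dropout: 283 × 0.7 = 198 and 253 × 0.7 = 177. The stated minimum of 253 per group gives 177 and 177.
- Weight: difference 1.25 kg, SD 4.
- Glucose: difference 0.2 mmol/l, SD 0.7.
- Alpha 5%. Sidedness is not stated, so both readings are computed.

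**Formula.** Power = Φ(d/SE − z), with SE = SD × √(1/n₁ + 1/n₂). z = 1.960 for a two-sided and 1.645 for a one-sided 5% test. Noncentral t values are given as a check.

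**Step 1: the article's figure, weight, 198/177, two-sided.** SE = 4 × √(1/198 + 1/177) = 0.414. d/SE = 1.25/0.414 = 3.02. Power = Φ(3.02 − 1.96) = 85.6% (t: 85.4%). This rounds to the published 86%.

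**Step 2: glucose, same assumptions.** SE = 0.7 × √(1/198 + 1/177) = 0.0724. d/SE = 0.2/0.0724 = 2.76. Power = Φ(2.76 − 1.96) = 78.9% (t: 78.7%).

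**Step 3: both outcomes, both arm sizes, both readings.**

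| Analysed | Test | Weight 1.25 kg | Glucose 0.2 mmol/l |
|---|---|---|---|
| 198/177 | two-sided 5% | 85.6% (t 85.4%) | 78.9% (t 78.7%) |
| 177/177 | two-sided 5% | 83.6% (t 83.4%) | 76.7% (t 76.4%) |
| 198/177 | one-sided 5% | 91.6% (t 91.5%) | 86.8% (t 86.7%) |
| 177/177 | one-sided 5% | 90.2% (t 90.1%) | 85.2% (t 85.0%) |

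Only the third row puts both outcomes at 86% or above.

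**Step 4: other routes to 86% for glucose with a two-sided test.**

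- Dropout applied as n/1.3 instead of n × 0.7: 80.5% (253 per arm) to 82.5% (actual arms). Still short.
- Dropout of 15% with the actual arms: 86.1%. No dropout: 89.5–91.0%. Both contradict the stated 30%.

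**Step 5: what 86% two-sided power would require.** z for 86% power is 1.080, so the multiplier is 1.960 + 1.080 = 3.040.

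- Detectable difference: 3.040 × 0.0724 = 0.22 mmol/l (0.23 with 177 per group).
- Or an SD of 0.2/(3.040 × √(1/198 + 1/177)) = 0.64 (0.62 with 177 per group).

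**Sensitivity to the SD** (two-sided, 177/177 to 198/177): SD 0.6 gives 88.0–89.7%; SD 0.5 gives 96.4–97.2%.

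**The case against.** The strongest defence is that the article never commits to a two-sided test. With a one-sided 5% test and the actual arms, which the text says were used, glucose has 86.8% and weight 91.6%. The stated lower bound then holds for both, with glucose as the binding outcome. On the two-sided reading even weight reaches 86% only by rounding 85.6%. This defence stands to the following extent: the stated inputs do not by themselves yield 77–79%, because two-sidedness has to be added to get there.

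The documents give the one-sided reading little support, however. No directional hypothesis or one-sided test is mentioned, and the effectiveness section speaks only of differences between groups. The p-values in Table 3 are two-sided: men's waist is 95.0 cm in both arms with p = 0.99, where a one-sided p would be near 0.5. Diastolic pressure of 83.3 against 82.7 (SD about 10) gives t of about 0.69, so p is about 0.49 two-sided and 0.25 one-sided; the table shows 0.51. These are baseline comparisons and do not settle how power was computed, but they show what an unqualified p-value means in this article.

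A second defence is that the cited SD may be too large. Table 3 shows a baseline fasting glucose SD of 0.5. If the follow-up SD were also 0.5 (an assumption), the SD of change would exceed 0.64 only if the baseline to follow-up correlation were below about 0.18. The planned mixed models may also gain precision over an unadjusted comparison. This is a fair reason to expect better real power, but it does not repair a calculation that cites 0.7.

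Finally, the calculation did not set the sample size, and 0.2 mmol/l is the low end of the cited range. Both points limit the consequences. Neither makes the statement correct on the conventional reading.

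**Conclusion.** The power statement is incomplete in a way that decides whether it is true. Under a two-sided 5% test, with the cited SDs and 30% dropout, it fits weight only (about 85–86%; 83–84% at 177 per group). Glucose has about 79% (76–77% at 177 per group), about 7–10 points below the stated bound. It holds for glucose only under an undisclosed one-sided 5% test with the actual arm sizes (86–87%), and at the stated minimum of 253 per group even that test gives 85%.

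A reader might infer more, and the documents do not support it:

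- That the inputs prove the glucose power is 77–79%. They do not, because sidedness is missing and one reading reproduces the published figure.
- That the weight result was computed and then attached to glucose. The numbers are compatible with this but do not show it.
- That the trial's real glucose power is 77–79%. That would need the SD of change to be 0.7 and the comparison to be unadjusted; with an SD of 0.6 the two-sided power is already 88–90%.
- That the trial is too small. The sample was fixed when the calculation was made, and the point concerns only how its power is reported.

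**What to change.** State the sidedness of the 5% alpha and report power separately for weight and glucose, each with its difference, its SD and the numbers analysed.

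- If the test is two-sided: weight 1.25 kg, about 85–86%; glucose 0.2 mmol/l, about 79% (198/177 analysed). Alternatively, give 0.22 mmol/l as the glucose difference detectable with 86% power.
- If the test is one-sided: say so explicitly (glucose about 87%, weight about 92%) and give the two-sided figures alongside.

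The authors know which test they used, so the correction should not presume it. The cost is one or two sentences and, on either route, a less favourable glucose figure in print. The design and the number of participants do not change.

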#### Effectiveness of the intensive lifestyle intervention

Statistical analysis will be performed according to the intention-to-treat principle and, if necessary, corrected for differences in background characteristics between the intervention and control groups. To assess the effect of the intervention program on the risk of diabetes and cardiovascular risk factors after 1 and 2 years, we will calculate differences between the intervention and control groups in general linear mixed models (GLMM). If we observe a difference between the intervention and control groups, we will examine whether the magnitude of the effect is most likely due to other cardiovascular risk factors or behavioral change. We will also use GLMM to examine the influence of baseline variables and the degree of participation (e.g., adherence and the actual carrying out of the components of the intervention) in weight reduction and behavioral changes. We will use multilevel analyses to distinguish group effects (e.g., effect of dietician’s work) from individual effects.

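### The stated power of 86% or more treats participants as independent although six dieticians deliver the intervention, and the planned dietician term is not tied to the between-arm comparison.

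*Protocol article*

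**What the plan says.** Delivery differs by arm. Under Individual lifestyle counseling, the article refers to "The six dieticians who will conduct the lifestyle counseling", with six to eight sessions in the first half year and three to four boosters over the following year and a half. Under Control group, participants are invited to "two group sessions led by student dieticians". Intervention participants are therefore grouped under six providers, and control participants have no counseling dietician.

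Under Size of the study population and the power calculation, the inputs are the recruited numbers (283 and 253, with 253 as the minimum per group), an SD of 4 kg for weight and 0.7 mmol/l for fasting plasma glucose (FPG), alpha of 5% and dropout of 30%. The conclusion is that "we have a power of 86% or more to demonstrate a minimum difference in weight reduction of 1.25 kg". The same power is claimed for an FPG difference of 0.2 mmol/l. No ICC, caseload or design effect is named.

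Under Effectiveness of the intensive lifestyle intervention, the between-arm differences come from general linear mixed models whose random effects are not listed. The paragraph then covers explanatory and adherence analyses. It closes with "We will use multilevel analyses to distinguish group effects", giving the dietician's work as the example of a group effect to be separated from individual effects.

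**The concern.** Participants counseled by the same dietician may have more similar outcomes than participants of different dieticians. With only six dieticians, each sees many participants, so even a small ICC raises the variance of the intervention-arm mean noticeably. The plan expects such an effect in its analysis section, while its power statement sets it to zero.

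The analysis text leaves a second gap. It plans a multilevel analysis but does not say that the treatment effect and its confidence interval come from it. An ordinary two-level model with dietician as the upper level has no value of dietician for the control arm, so the word multilevel does not by itself settle which model is meant. At stake are how far the stated power can be relied on and, if the term were left out, the width of the interval for the main comparison.

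**Working it through.** **Inputs from the protocol article.** Intervention 283, control 253, dropout 30%: 283 × 0.7 = 198.1 and 253 × 0.7 = 177.1 retained. Weight: difference 1.25 kg, SD 4. FPG: difference 0.2 mmol/l, SD 0.7. Alpha 5%, sidedness not stated. Six dieticians.

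**Assumptions not in the article.** Even caseloads, m = 198.1/6 = 33.0. Dietician ICC of 0.01, 0.02 or 0.05. Total variance held fixed. Clustering in the intervention arm only.

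**Step 1: reproduce the stated figure, independent participants.**

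SE = SD × √(1/177.1 + 1/198.1); power = Φ(difference/SE − z).

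- Weight: SE = 0.414, ratio 3.02. Two-sided power Φ(3.02 − 1.96) = 85.6%; one-sided Φ(3.02 − 1.645) = 91.6%.
- FPG: SE = 0.0724, ratio 2.76. Two-sided 78.9%; one-sided 86.8%.

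The 86% is thus the two-sided figure for weight; a one-sided test is needed for it to hold for both outcomes. On either reading it comes from the independent-participant formula, with no allowance for clustering.

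**Step 2: allow for dieticians in the intervention arm.**

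Design effect DE = 1 + (m − 1) × ICC = 1 + 32 × ICC; SE = SD × √(1/177.1 + DE/198.1).

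| ICC (assumed) | DE | SE relative to Step 1 | Weight, two-sided | FPG, two-sided | Weight, one-sided | FPG, one-sided |
|---|---|---|---|---|---|---|
| 0 | 1.00 | 1.00 | 85.6% | 78.9% | 91.6% | 86.8% |
| 0.01 | 1.32 | 1.07 | 80.4% | 73.1% | 88% | 82% |
| 0.02 | 1.64 | 1.14 | 75.4% | 67.8% | 84% | 78% |
| 0.05 | 2.60 | 1.32 | 62.6% | 55.0% | 74% | 67% |

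Example, weight at ICC 0.02: SE = 4 × √(1/177.1 + 1.64/198.1) = 0.472; 1.25/0.472 = 2.65; Φ(2.65 − 1.96) = 75.4%.

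**Step 3: few clusters.** The normal approximation is generous with six dieticians. A Satterthwaite approximation that gives the intervention-arm variance 5 degrees of freedom yields two-sided weight power of about 76% / 69% / 54% at ICC 0.01 / 0.02 / 0.05. The same formula gives about 82% at ICC 0, so part of this further fall comes from the approximation itself. The Step 2 figures are the ones to rely on.

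**Step 4: if the dietician term were left out of the main comparison.** Type I error = 2 × [1 − Φ(1.96/SE ratio)] = 6.8% / 8.6% / 13.9% at ICC 0.01 / 0.02 / 0.05. This refers to the null that the average effect over a population of dieticians is zero while dieticians differ from one another. If the intervention has no effect on anyone, dieticians add no outcome variance. Sorting individually randomized participants into caseloads then leaves the variance of the arm mean unchanged, and the error stays at 5%.

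**The case against.** A reader might infer that the main comparison treats participants as independent, so that its standard errors will be too small. The article does not support this. The arm difference comes from a mixed model, and the same paragraph plans multilevel analyses with the dietician as the named example. That these are separate from the between-arm comparison is only an inference. It is also fair to say that a condensed article may leave the exact random effects and degrees of freedom to a fuller plan. This part of the objection stands: the point about the model is a request for clarity, and the type I figures are conditional.

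The size of the loss can also be questioned. No ICC is given and equal caseloads are assumed. Participants are offered an exercise program run by other staff as well, which may dilute clustering by dietician. The 1.25 kg target lies below the 1.5–3 kg that the article cites from previous studies; at 1.5 kg the Step 2 formula gives 92% / 89% / 78%. Recruitment is complete, so a restated power changes no sample size. All of this limits the practical weight of the point.

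What the objection does not remove is the inconsistency within the printed text. The article computes a power figure, states it as a floor, and expects a source of variance that the figure omits.

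**Conclusion.** The power statement is too favourable for any positive dietician ICC, and the article itself expects a dietician effect. Under the assumptions above, two-sided weight power is about 80% / 75% / 63% instead of 85.6%, and FPG power about 73% / 68% / 55% instead of 78.9%. On a one-sided reading the weight figure still exceeds 86% at ICC 0.01, but the FPG figure does not. The direction is certain if the ICC is above zero; the size depends on the assumed ICC and on even caseloads.

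On the analysis, the finding is only that the dietician level is not tied to the between-arm comparison. Type I error of about 7% / 9% / 14% would follow only if the term were omitted, dieticians truly differed in effect, and the assumed ICC and caseloads applied. It is not a property of the plan as written. Household members assigned together (38 people, under Study design) are a further dependence missing from the power figure, probably a small one. It is not included in these figures.

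**What to change.** State that the primary treatment effect and its confidence interval come from a partially nested mixed model, with a random dietician effect in the intervention arm only and small-sample degrees of freedom (Satterthwaite or Kenward-Roger). Restate the power as a range over plausible ICCs, for example 0.01 to 0.05, and give the sidedness of the test with it.

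No change in enrolment is needed. The costs are somewhat wider intervals and a less favourable stated power. The team must also confirm that each participant's dietician is recorded: the process evaluation mentions dieticians' files but does not list that item.
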